### Sample size

The sample size calculation is based on the between-group difference for the primary outcome, the global relationship quality score from the EAS, which ranges from 0 (worst relationship possible) to 100 (best relationship possible). Based on a previous RCT conducted by our team in 67 families of children with an NDD (CP),^24^ we assume the SD of the Global EAS will be 14.3 units, and that identifying a difference between the active (PACT) and waitlist control group of 5.0 units is clinically important. This is equivalent to a between-group difference of 0.35 SD. To achieve 80% power, 258 families (129 in each group) are required to provide outcome data (alpha=0.05). To allow for expected 11%–15% participant attrition (as experienced in our previous trials),^24^ we will recruit a total of 300 families into this RCT. Participant retention strategies will be guided by the consumer engagement panel and will include a quarterly study update. Sample size calculations were conducted using Stata statistical software V.14 (StataCorp, College Station, Texas).

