### Statistical analysis of primary and secondary outcomes

The primary outcome will be analysed using mixed-model repeated-measures linear regression (multilevel modelling) with time (T1, T2, T3) and group (*PACT Online*/CAU) included as the main effects, and a time-by-group interaction term. Child will be included as a random effect to account for the repeated measures from each participant. Secondary comparisons will be conducted using linear models for continuous outcomes, logistic regression models for binary outcomes and Poisson models for count outcomes. The value of the outcome variable at baseline will be included as a covariate when appropriate. When repeated measures are analysed, the non-independence of results from the same family will be accounted for using mixed-effects models. Subgroup analyses will compare outcomes by child age and child diagnosis. Analysis will follow standard principles for RCTs with two-group comparisons using the intention-to-treat principle. In the event that >10% of outcomes are missing, we will conduct a sensitivity analysis to investigate the sensitivity of results. The pattern of missingness will be examined, and if the data are ‘missing at random’, we will use multiple imputation by chained equations, whereas if the data are determined to be ‘missing not at random’, we will use pattern mixture models.

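### The missing-data rule runs the pattern-mixture analysis only if the data are found to be missing not at random, which observed data cannot establish

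*Protocol article*

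**What the plan says.** All of this is in the protocol article. The section Statistical analysis of primary and secondary outcomes fixes three things.

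- Primary model: "The primary outcome will be analysed using mixed-model repeated-measures linear regression (multilevel modelling) with time (T1, T2, T3) and group", with a time-by-group interaction and child as a random effect.
- Trigger: "In the event that >10% of outcomes are missing, we will conduct a sensitivity analysis to investigate the sensitivity of results".
- Choice of method: "The pattern of missingness will be examined, and if the data are ‘missing at random’, we will use multiple imputation by chained equations"; and "if the data are determined to be ‘missing not at random’, we will use pattern mixture models".

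The section Sample size bears on how likely the trigger is: "To allow for expected 11%–15% participant attrition", the plan is that "we will recruit a total of 300 families into this RCT". It does not say whether that attrition refers to 12 weeks (T2, the primary time point) or to 6 months (T3). No other analysis that relaxes MAR is mentioned.

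**The concern.** MAR and MNAR differ only in how the unseen outcomes are distributed given the seen data. Looking at who dropped out, when, and with what baseline values can contradict missing completely at random. It cannot tell MAR from MNAR. The rule therefore asks for a finding that the data cannot supply.

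The mixed model, if fitted by likelihood as is usual, is already valid under MAR. An analyst who follows the text and finds no proof of MNAR will run MICE, which rests on the same kind of assumption. Pattern-mixture modelling, the one named method that relaxes it, waits on a condition that cannot be met. At stake is the robustness statement: the report could call the T2 result robust to missing data when departures from MAR were never examined. The rule also leaves room to choose the method after seeing the data.

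**Working it through.** **1. The plan's own figures.** Inputs from Sample size: difference 5.0, SD 14.3, alpha 0.05 (taken as two-sided), power 80%.

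n per arm = 2 × (1.96 + 0.842)² × 14.3² / 5.0² ≈ 128.4, rounded up to 129, so 258 in total. This reproduces the stated figure. 258 / 300 = 0.86, so recruiting 300 allows for 14% attrition, inside the stated range.

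**2. How likely is the trigger?** More than 10% of 300 means at least 31 families missing. If families drop out independently with probability d, the binomial tail gives:

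| True attrition d | P(at least 31 of 300 missing) |
|---|---|
| 11% | 0.67 |
| 13% | 0.93 |
| 14% | 0.98 |
| 15% | 0.99 |

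If the stated range describes attrition to T3, missingness at T2 could be lower, and so could these probabilities for the primary time point.

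**3. Does MICE under MAR test the assumption?** Simulation with 150 per arm, true effect 5, SD 14.3 and 1,000 runs. The baseline correlation of 0.6 and the dropout models are assumptions, not document figures. The likelihood analysis was simplified to T2 regressed on baseline and group, and the imputation used the same variables.

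| Dropout | Missing | Likelihood analysis | Multiple imputation | Full data |
|---|---|---|---|---|
| Depends on baseline (MAR) | 14.3% | 5.05 | 5.05 | 5.02 |
| Depends on T2 outcome in PACT (MNAR) | 14.8% | 6.33 | 6.33 | 4.92 |

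In the MNAR case both are too high by 6.33 − 4.92 = 1.41 units. The two estimates correlate at about 0.996 and differ by about 0.1 unit on average. Agreement between them says nothing about MNAR.

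**4. Size of a departure (illustration only).** Assume an effect of 5.0 under MAR, a fraction m of PACT outcomes missing, and missing PACT outcomes worse than MAR predicts by a shortfall s, with CAU unchanged. Then effect = 5.0 − m × s.

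- m = 0.15, s = 5: 5.0 − 0.75 = 4.25
- m = 0.15, s = 10: 5.0 − 1.5 = 3.5

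Unadjusted SE at 129 per arm = 14.3 × √(2/129) = 1.78; critical difference = 1.96 × 1.78 = 3.49.

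For the T2 time-by-group contrast, SE ≈ 1.78 × √(2(1 − r)), where r is the correlation of T1 with T2, which the document does not give:

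- r = 0.4: SE 1.95, critical difference 3.8
- r = 0.7: SE 1.38, critical difference 2.7

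So 4.25 exceeds the critical difference throughout, while 3.5 lies within the range 2.7 to 3.8.

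**5. Tipping point on the unadjusted SE.** With 150 × (1 − m) per arm, s = (5.0 − 1.96 × SE) / m:

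- m = 0.15: SE 1.791, s = (5.0 − 3.510) / 0.15 ≈ 9.9 units
- m = 0.11: SE 1.750, s = (5.0 − 3.431) / 0.11 ≈ 14.3 units

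**The case against.** The strongest reply is that this rule governs only a sensitivity analysis. The primary model, sample size and conduct are untouched, and a suitable method is already named, so only the condition attached to it is at fault. That stands and limits the weight of the point.

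Four stronger readings are tempting, and the document does not support them.

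- *The rule is certain to apply.* It is likely, not certain: 0.67 at the low end of the range, and the attrition time point is not given.
- *The plan has no real sensitivity analysis.* MICE can draw on collected variables outside the primary model, such as diagnosis, age or parent-reported outcomes. That can make MAR more plausible and change the estimate. The near-identity in the simulation holds for imputation with the same variables. Even so, a richer imputation model does not examine MNAR.
- *Dropout will differ by arm.* Sample size gives one overall range and no split. Participants are unblinded, and CAU families are offered the programme only after T3, so differential or outcome-related dropout is possible. It is not shown.
- *A plausible departure would overturn the result.* The near-match of 3.5 with 3.49 comes from an unadjusted SE and an assumed 10-unit shift in PACT alone. That shift is 0.7 SD (10 / 14.3) and twice the target difference, and nothing in the document supports it. A 5-unit shortfall leaves the result significant across the correlations tried.

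**Conclusion.** The point holds as an error in stated text, not as missing detail: the article itself fixes a decision rule that cannot be carried out, and an analysis plan that followed it would inherit the fault. The likely outcome is MICE alone, which leaves the MAR assumption of the primary T2 comparison unexamined.

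That conclusion assumes the mixed model is fitted by likelihood. The trigger probabilities assume independent dropout at the stated rates. The effect shifts (5.0 to 4.25 or 3.5) and the simulated bias of about 1.4 units rest on assumptions not in the document. They show what an unexamined departure could do, and do not forecast this trial's result. The primary estimate and the sample size are not in question.

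**What to change.** In Statistical analysis of primary and secondary outcomes:

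1. Delete the condition that the data be determined to be missing not at random.
2. State that the primary mixed model takes MAR as its working assumption.
3. Report the already-named pattern-mixture analysis for the T2 observed EAS outcome whatever inspection of the missingness shows. Pre-specify the shifts and let them differ by arm, for example delta-adjusted imputation carried to a tipping point.
4. MICE with auxiliary variables may stay as a supplementary MAR analysis. Measures of programme attendance cannot simply enter a common imputation model, because CAU families have none before T3. Reference-based imputation is optional.

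The change should be made before outcomes by arm are seen. It costs revised wording and a few hours of programming, with no new data. The downside is a possibly less favourable robustness statement.

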#### Health economics evaluation

The primary purpose of economic evaluation will be to conduct a cost and consequence analysis (CCA) to guide the allocation of resources for implementation, with CCA the chosen approach because the intervention has multiple health and non-health outcomes that are hard to measure in a single unit. CCA will assess a wide range of important health outcomes to assess the value for money of the intervention. The study will look at the incremental differences in various health outcomes between the intervention and CAU and present a comprehensive summary.

#### Implementation analysis

Qualitative analyses will be conducted on (1) semistructured interviews with a subgroup of *PACT Online* participants and (2) semistructured interviews with therapists delivering PACT Online, (3) semistructured interviews with stakeholders in partner organisations and (4) a randomly selected subset of clinician notes. The CFIR, a meta-theoretical framework synthesising implementation theories, will be used to inform coding and analysis with a focus on ensuring that (1) *PACT Online* is acceptable and appropriate for parents, meeting their needs and (2) the contextual factors shaping implementation in existing health, educational and disability services are understood, with appropriate implementation strategies developed. For example, parents will be asked what the best, worst and most difficult parts of PACT Online were, what changes they have noticed, whether or not they found PACT Online inclusive and how they think PACT Online could best be implemented outside a trial. Analysis will be led by two independent qualitative researchers, drawing from reflexive thematic analysis principles.^52^

### Outcomes and significance

It is anticipated that this project will have a lasting impact on the health and well-being of children with NDD and their families through the delivery of an innovative online allied health intervention targeting the parent–child relationship and parenting. If successful, *PACT Online* will be sustainably embedded in existing health services for families of children with NDD, growing parent empowerment and better supporting parents, with long-term flow on effects for parent and child.

## Ethics and dissemination

Ethical approval has been obtained from the University of Queensland, Human Research (Ethics Approval 023/HE000040) and the study has been registered with the Australian New Zealand Clinical Trials Registry (ACTRN12623000612617) since 5 June 2023. PACT Online will be offered to the CAU group after T3 follow-up for ethical reasons and to maintain participant engagement. As a consequence, testing downstream benefits beyond 6 months will not be possible. Dissemination of study outcomes will occur through published papers in scientific journals, presentations at conferences and to study participants through the study update. If *PACT Online* is effective, the *PACT Online* intervention will be released as a massive open online course. The implementation analysis will result in the identification of contextual factors influencing implementation and the development of tailored implementation strategies.

Should the intervention be effective, this trial will contribute crucial evidence to support implementation of the *PACT Online* intervention for families of children with a disability, including informing cost-effectiveness through our health economic analysis. This is supported by our implementation plan and partners in the community, which will facilitate rapid uptake of findings and cross-sector collaborations between primary healthcare professionals, families of children with NDD and health policymakers.
